### Interim analyses {21b}

Data will be reviewed by the data monitoring committee (DMC) after first ten liver perfusions. If there are no safety concerns, recruitment will continue as per the study protocol.

The DMC or sponsor may recommend suspension or termination of the study either at an individual investigation site or the entire study for significant and documented reasons. An investigator and ethics committee may suspend or prematurely terminate participation in the study at the investigation sites for which they are responsible. If suspicion of an unacceptable risk to subjects arises during the study, or when so instructed by the ethics committee, the sponsor shall suspend the study whilst the risk is assessed. The sponsor shall terminate the study if an unacceptable risk is confirmed.

The sponsor shall consider terminating or suspending the participation of a particular study site or investigator in the study if monitoring or auditing identifies serious or repeated deviations on the part of an investigator.

If suspension or premature termination occurs, the terminating party shall justify its decision in writing and promptly inform the other parties with whom they are in direct communication. The chief investigator and sponsor shall keep each other informed of any communication received from either the ethics committee.

If, for any reason, the sponsor suspends or prematurely terminates the study at an individual investigation site, the sponsor shall inform the Ethics Committee, either through the chief investigator or the sponsor. If the suspension or premature termination was in the interest of safety, the sponsor shall inform all other investigators.

If suspension or premature termination occurs,the sponsor shall remain responsible for providing resources to fulfil the obligations from the study protocol and existing agreements for following up the subjects enrolled in the study, andthe chief investigator or authorised designee shall promptly inform the enrolled subjects at his/her study site, if appropriate.

### Methods for additional analyses (e.g. subgroup analyses) {20b}

There are no plans for additional subgroup analyses.

### Methods in analysis to handle protocol non-adherence and any statistical methods to handle missing data {20c}

#### Procedure for accounting for missing, unused, and spurious data

Withdrawals from the trial after implantation will be documented, and a narrative analysis of withdrawals will be performed. Recipients withdrawing from the trial after implantation will be included in analysis using all available data. Consideration will be given to model-based and multiple imputation methods and detailed in the SAP. The rational for this is briefly described below.

The primary outcome will be available for all livers randomised and perfused. Missing data will be described and reported, although it is anticipated very few patients will be lost to follow-up. The reason for missingness for variables implicated in the primary analyses will be explored through regression of the missing variable indicator on other observables and detailed in the SAP. All analyses will include all data available.

The small sample size poses significant limitations for building robust multiple imputation models for handling missing data. Consideration of multiple imputation model will be given only for the analyses of selected/primary outcomes when it is valid to do so:The proportion of missing data is less than 5% and the impact of missing is negligibleWhen no additional information can be obtained (no auxiliary variables to use for imputation can be identified)When missing data can be assumed to be missing completely at random from the outsetWhen missingness can be assumed missing at random conditional on other observable data

In the case where the primary outcomes are not missing at random, then a ‘worst-best-case’ scenario sensitivity analyses will be undertaken to show the range of uncertainty due to missing. Briefly, in such analyses, a ‘worse-best-case’ scenario dataset will be generated where it is assumed that all participants missing the primary outcome in one group had a harmful outcome and all missing the outcome in the other group had a beneficial outcome.

### Plans to give access to the full protocol, participant level-data and statistical code {31c}

Direct access will be granted to authorised representatives from the sponsor and the host institution to permit trial-related monitoring, audits and inspections.

## Oversight and monitoring

### Composition of the coordinating centre and trial steering committee {5d}

#### Trial management group (TMG)

A TMG comprising the CI, other lead investigators, local principal investigators and members of the CTU. The TMG will be responsible for the day-to-day running and management of the trial. It will meet at least twice a year, more often during set-up and close down phases of the trial. At least one face-to-face meeting will be held each year.

#### Trial steering committee (TSC)

The role of the TSC is to:provide expert oversight of the trialmaintain confidentiality of all trial information not already in the public domainmake decisions as to the continuation of the trialmonitor recruitment rates and advise the TMG on recruitment issuesreview and approve V1.0 of the protocol and any substantial amendmentsreview regular progress reports of the trial from the trial teamreceive feedback from the DMC and consider their recommendations, including any ethical implications arising from their adviceassess the impact and relevance of any accumulating external evidencemonitor completion of case report forms (CRFs) and comment on strategies from TMG to deal with problemsmonitor protocol deviations and advise the TMG on remedial actionmonitor any quality issues, e.g. serious breaches and advise TMG on remedial action approve additional sub-studiesoversee the timely reporting of trial resultsapprove the statistical analysis planapprove the publication policyapprove the main trial manuscriptapprove abstracts and presentations of results during the trial and on completionapprove any requests for release of data or samples including clinical data and stored biological samples

The ultimate decision on continuation of the trial lies with the TSC.

### Composition of the data monitoring committee, its role and reporting structure {21a}

#### Safety monitoring committee

The trial has a data monitoring committee (DMC) which consists of at least three independent members, including clinicians with relevant expertise and a statistical expert, independent from the Investigators and the funding source. The DMC will periodically review accruing data to safeguard the interests of the trial participants, potential participants and future patients and assess the safety of the interventions. As a result of the reviews, the DMC may make recommendations to the TSC, including premature termination of the trial, should they feel it is indicated.

A separate DMC charter will contain full details of the committee and its roles and reporting structure.

### Adverse event reporting and harms {22}

#### Safety reporting

Adverse event definitions are provided in Table 5. The below sections describe the required reporting for adverse events within the clinical trial. This is in addition to the standard incident reporting to the device manufacturer and to clinical governance at NHSBT. It is a statutory condition of a licence for procurement or transplantation activity to rapidly report to NHSBT (acting on behalf of the HTA), relevant and necessary information concerning adverse events which may influence the quality and safety of organs. All study sites will therefore follow their usual procedures for highlighting concerns—by completing an NHSBT incident submission form: https://safe.nhsbt.nhs.uk/IncidentSubmission/Pages/IncidentSubmissionForm.aspx.

**Table 5 Tab5:** Adverse event definitions

Adverse event (AE)	Any untoward medical occurrence, unintended disease or injury or untoward clinical signs (including abnormal laboratory findings) whether or not related to the study intervention.
Serious adverse event (SAE)	An adverse event that: • Led to death • Resulted in serious deterioration in the health of the subject that: ◦ resulted in a life-threatening illness or injury ◦ resulted in a permanent impairment of a body structure or a body function ◦ required in-patient care or prolongation of hospitalisation ◦ resulted in persistent or significant disability or incapacity ◦ resulted in congenital anomaly or birth defect ◦ resulted in medical or surgical intervention to prevent life-threatening illness or injury or permanent impairment to a body structure or a body function. This includes device deficiencies that might have led to a serious adverse event if: a) suitable action had not been taken or b) intervention had not been made or c) circumstances had been less fortunate

These reports will be reviewed periodically by the data monitoring committee (DMC). A safety review will be conducted by DMC after the first ten liver perfusions. All available data will be reviewed with a focus on adverse events, graft and patient survival, as well as organ utilisation.

Untoward incidents related to the process of organ retrieval and transplantation is routinely collected by NHSBT. Further detail may be found here: http://www.odt.nhs.uk/odt/governance-and-quality/incident-reporting/.

#### Severity definitions

The following definitions will be used to determine the severity rating for all adverse events:Mild: awareness of signs or symptoms that does not interfere with the subject’s usual activity or is transient that resolved without treatment and with no sequelae.Moderate: a sign or symptom, which interferes with the subject’s usual activity.Severe: incapacity with inability to do work or perform usual activities.

NB: to avoid confusion or misunderstanding of the difference between the terms ‘serious’ and ‘severe’, the following note of clarification is provided: ‘severe’ is often used to describe intensity of a specific event, which *may* be of relatively minor medical significance. ‘Seriousness’ is the regulatory definition supplied above.

#### Anticipated adverse events

As liver transplant recipients, all recruits to the DeFat trial are at high risk of experiencing AEs due to the complexity of their condition. Many of these events are anticipated as a result of the patient’s medical condition and standard treatment received in hospital. We will only document adverse events if in the opinion of the investigator they are likely to be associated with the trial intervention.

All adverse events meeting the definition of serious adverse event will be recorded.

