## Objectives {7}

The experimental data outlined above suggest that the combination of NMP and defatting may be effective in reducing the fat content of livers and improving perfusion parameters to meet functional criteria for transplantation. In this first clinical study, the primary objective is to confirm the safety and assess efficacy of the NMP-defatting protocol in steatotic donor livers intended for transplant. The secondary objective is to test the feasibility of the (i) inclusion criteria (false positives and negatives); (ii) delivery of intervention and (iii) the study endpoints. These objectives will provide information of likely effect sizes in order to design a subsequent phase III study in the future.

The mechanistic studies will be analysed subsequent to the main clinical outcomes. These will be carried out for two broad reasons (i) to identify more sensitive and specific markers of transplantability and (ii) to understand the process of defatting that leads to a steatotic organ being reconditioned. The proposed mechanistic studies and associated outcome measures are described in the outcome section of this protocol.

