### Plans to promote participant retention and complete follow-up {18b}

The follow-up visits for the DeFat study align with routine clinical visits. All patients completing the 6-month follow-up assessment will be regarded as having completed the primary study. All patients will be encouraged to complete study follow-up, and all reasonable efforts will be made to ensure completeness of follow-up. Measures include ensuring that sample collection and assessments are made, where possible, at routine hospital visits rather than additional appointments and that patients do not incur extra financial costs (e.g. travelling costs) as a result of study participation.

It is understood that study participants may withdraw consent for study participation at any time irrespective of their reasons. The investigators may also withdraw a recipient from the study in order to protect their safety and/or if they are unwilling or unable to comply with the required study procedures. We will keep all data accrued to the point of withdrawal, as is stipulated in the trial consent form.

Possible reasons for investigator-led withdrawal of a participant from the trial include:Major protocol deviationWithdrawal of consentLoss to follow-upSAE/SUSAREarly termination of study

In the event of a patient withdrawing from the trial, the reason for withdrawal must be documented on the eCRF. Such patients will be asked whether they consent to the use of ongoing data collected as standard in the national transplant registry for the purposes of this study.

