#### Assessment of causality

The relationship of each adverse event to the trial procedures, conduct or intervention must be determined by a medically qualified individual according to the following definitions:

Related: the adverse event follows a reasonable temporal sequence from the trial procedures, conduct or intervention. It cannot reasonably be attributed to any other cause.

Not related: the adverse event is probably produced by the participant’s clinical state or by other modes of therapy administered to the participant.

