#### Procedures for reporting adverse events

It is the responsibility of the local investigator to ensure that all adverse events considered related to the intervention and occurring during the course of the study are recorded. This will include but not be limited to:A description of the eventThe dates of the onset and resolutionAction takenOutcomeAssessment of relatedness to the trial procedures, conduct or interventionWhether the AE is serious or not

Whether the AE arises from errors in OrganOx *metra*^*®*^ device functioning or use, adverse events that occur during the course of the study should be treated by established standards of care that will protect the life and health of the study subjects.

Adverse events considered related to the intervention should be recorded on the eCRF via the MACRO database provided. If the eCRF is unavailable for any reason, a paper version of the form should be completed.

The severity of events will be assessed on the following scale: 1 = mild, 2 = moderate, 3 = severe.

Non-serious AEs, considered related to the trial procedures, conduct or intervention as judged by a medically qualified investigator or the sponsor, will be followed up until resolution.

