#### Reporting procedures for serious adverse events

It is the responsibility of the local investigator to ensure that all adverse events which fall in to the category of serious adverse events (SAEs) are reported to NHSBT Clinical Trials Unit, chief investigator, central investigators and, if required, to their local R&D department as soon as possible after becoming aware of the event but no later than 24 h. This will include but not be limited to:A description of the eventThe dates of the onset and resolutionAction takenOutcomeAssessment of relatedness to the trial procedures, conduct or intervention

Serious adverse events will be collected from transplant until 6 months following the transplant, via a purposely designed MACRO database (access via www.ctu.nhsbt.nhs.uk/macro). SAEs will be automatically notified to NHSBT CTU. If the eCRF is unavailable for any reason, a paper version of the form should be completed, scanned and emailed to [contact]. Within the following five working days, the local investigator may be required to provide additional information on the SAE in the form of a written narrative. This should include a copy of the completed SAE form, and any other diagnostic or relevant information that will assist the understanding of the event.

Additional and further requested information (follow-up or corrections to the original case) should also be added to eCRF using a new SAE Report Form. NHSBT CTU will ensure that all SAEs are reported to the sponsor.

The clinical reviewers will review the SAEs and, if they agree that the SAEs are unexpected and related, or pose an immediate risk to patient health or safety, then they will report them to the DMC immediately and to the device manufacturer and the REC within 15 calendar days of the chief investigator becoming aware of the event. The DMC will review the accumulating data at regular intervals.

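### Safety is part of the primary objective, but the rules for recording harms conflict, SAE collection opens only after the intervention has been delivered, and an SAE may prompt withdrawal

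*Protocol article*

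**What the plan says.** The Objectives section of the protocol article makes safety one half of the primary aim: "the primary objective is to confirm the safety and assess efficacy of the NMP-defatting protocol in steatotic donor livers intended for transplant". The primary outcome section repeats this.

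On how harms are recorded, the article says:

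- **Anticipated adverse events:** "We will only document adverse events if in the opinion of the investigator they are likely to be associated with the trial intervention". The same section then exempts serious events: "All adverse events meeting the definition of serious adverse event will be recorded".
- **Procedures for reporting adverse events:** the local investigator must ensure that "all adverse events considered related to the intervention and occurring during the course of the study are recorded". Severity is scored 1 to 3.
- **Assessment of causality:** besides plausible timing, a related event must meet this condition: "It cannot reasonably be attributed to any other cause". The only other category is not related.
- **Trial design, Secondary outcome measures, the safety outcome list and Table 4:** adverse-event details at each visit; infection, rejection, biliary and vascular complications and reoperation, graded by Clavien–Dindo; and a line for any further adverse event reported. None of these carries a causality condition.
- **Reporting procedures for serious adverse events:** "Serious adverse events will be collected from transplant until 6 months following the transplant".
- **Safety reporting, Table 5, SAE definition:** "This includes device deficiencies that might have led to a serious adverse event if", followed by three hypothetical circumstances.
- **Participant retention:** "Possible reasons for investigator-led withdrawal of a participant from the trial include", and the list that follows contains SAE/SUSAR and major protocol deviation.

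**The concern.** A safety comparison between arms needs each event counted by the same rule in both arms, over a window that covers the exposure, with follow-up that does not depend on the outcome. The article departs from each of these in part. Sites receive two incompatible recording instructions, so the rate of a non-serious event could depend on which section a site follows. The SAE window opens after the exposure has ended. An adverse outcome is itself listed as grounds for ending participation.

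At stake are the completeness of the non-serious harms data, the formal reporting of events during perfusion, and later follow-up of the recipients who fare worst. The DMC review after ten perfusions is to focus partly on adverse events, so it depends on the same capture.

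**Working it through.** **1. The plan's own figure.** The only design calculation concerns the efficacy endpoint: 30 livers per arm, 65% against 95%, 5% significance, power above 80%. With a two-sided test and pooled variance under the null, the null standard error is √(2 × 0.80 × 0.20 / 30) = 0.1033 and the alternative standard error is √((0.65 × 0.35 + 0.95 × 0.05) / 30) = 0.0957. Power is Φ((0.30 − 1.96 × 0.1033) / 0.0957) = 84.6%. The stated figure reproduces and has no bearing on safety. The article gives no safety event rate, margin or power, so the rest is a comparison of sections.

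**2. Recording rule.** Table 5 defines an adverse event irrespective of relatedness, so a treated infection is an adverse event. The safety outcome list requires it to be recorded. The rule for anticipated events would leave it out if it is non-serious and not judged related, and that rule does not exempt the listed outcomes. Both instructions cannot be followed.

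**3. Threshold.** The anticipated-events section asks whether an association is likely. The causality section asks that no other cause be reasonable. The second test is stricter, and its two categories leave no place for a merely possible relationship.

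**4. Severity scale.** The outcome sections use Clavien–Dindo. The severity section applies mild, moderate and severe to all adverse events, and the reporting section codes these 1 to 3. No section says which scale governs a listed complication.

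**5. SAE window.** The intervention is delivered during perfusion, and the liver is flushed before implantation. A device deficiency during perfusion can meet Table 5's SAE definition before collection opens. Table 3 likewise marks safety outcomes only from post-reperfusion onwards. If a randomised liver is discarded and not transplanted, no SAE window opens for it. Such events would appear as discards or device failures, outside the 24-hour SAE route.

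**6. Withdrawal.** By the time a recipient has a post-transplant SAE, the intervention is complete. Withdrawal cannot reduce exposure to it, but can end later trial assessments. Data up to withdrawal are kept and analysed; later registry data require the patient's agreement.

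**7. Effect of the filter.** Let the true risks of an unlisted non-serious event be p₁ and p₂, and let a fraction f be judged related, equally in both arms. The recorded risks are f·p₁ and f·p₂, so the risk difference shrinks to f·(p₂ − p₁) while the expected ratio is unchanged. As an illustration of direction only, take assumed risks of 40% and 70%, which have no source in the article, and 30 recipients per arm, which supposes that every liver is transplanted. The step 1 formula gives power of 65% at f = 1, 25% at f = 0.5, 13% at f = 0.25 and 7% at f = 0.1. This applies to neither SAEs nor listed complications recorded as the outcome sections require.

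**The case against.** A reader might infer that safety cannot be compared between arms at all. The documents do not support that:

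- All SAEs after transplant are recorded whatever their cause. Table 5's definition is broad and includes prolonged hospitalisation, so many important complications would qualify.
- Infection, rejection, biliary and vascular complications, reoperation, primary non-function, post-reperfusion syndrome, renal replacement, and graft and patient survival are prespecified for both arms.
- The perfusion phase is not unobserved. Discard rate, perfusate culture and device failures are safety outcomes, discard reasons are collected from randomisation, and NHSBT incident reporting runs in parallel.
- Withdrawal after an SAE is possible, not required. The SAE that prompted it is already in the data, withdrawn recipients are analysed with what is available, and missing outcomes may be sought from the registry.
- Local teams are blinded, which limits differential attribution. The likely effect of the filter is under-recording in both arms.

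All of this stands and confines the point. It does not remove the contradiction between the recording rules, the mismatch between the SAE window and Table 5, or the risk of outcome-dependent loss of later follow-up, which registry linkage offsets only in part.

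**Conclusion.** The point holds in a limited form. Followed as written, the rules allow non-serious listed complications to be omitted at some sites, permit comparison of unlisted non-serious events only through an attribution filter, leave SAE-type events during perfusion outside the SAE route, and risk losing later follow-up because of the outcome.

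Post-transplant SAEs, primary non-function, and graft and patient survival remain comparable by arm. So do the named complications, provided sites follow the outcome lists.

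The size of the under-recording cannot be derived from the article, and the conclusion rests on none of the illustrative rates. It rests on reading the sections as sites would receive them, with no further guidance shown. Because safety is in the primary objective and the correction is cheap, the sections should be reconciled.

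**What to change.** Amend the protocol wording and site guidance to:

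1. State that the safety outcomes in the secondary outcome section and safety outcome list are recorded for every recipient regardless of causality, on the Clavien–Dindo scale. Apply the relatedness rule and the 1–3 scale only to additional non-serious adverse events.
2. Use one causality threshold, reconciling the anticipated-events and causality sections.
3. Start SAE and device-deficiency collection at randomisation or start of perfusion, so that the window matches Table 5, and align Table 3.
4. State that an SAE or protocol deviation does not by itself end outcome data collection, which continues unless consent is withdrawn.

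The cost is a protocol amendment and slightly more eCRF entry, largely for events already in routine notes.
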